**Methods:**

To examine SSRI response and the role of 5-HT, this study will employ a randomised double-blind within subject, repeated measures design, recruiting adolescent patients with major depressive disorder. Participants will be subjected to acute tryptophan depletion (ATD) and the balanced control condition on two separate study days within a first study phase (Phase A), and the order in which these conditions (ATD/balanced control condition) occur will be random. This phase will be followed by Phase B, where participants will receive open label pharmacological treatment as usual with the SSRI fluoxetine and followed-up over a 12-week period.

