### Trial design

In Phase A, this study will use a randomised, double-blind, within subject repeated measures design. During this phase, participants will undertake the challenge procedures (either ATD or balanced control condition (BAL)) on two separate study days, spaced at a maximum of 7 days apart. In Phase B, this study will employ an open label fluoxetine treatment for a period of 12 weeks.

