#### Phase B

Phase B will commence between 24 and up to a maximum of 72 h after the second day of Phase A. Phase B will consist of a 12-week open label pharmacological treatment as usual with the SSRI fluoxetine. Participants will be required to attend weekly follow-up sessions with the study doctors. Fluoxetine will be prescribed and administered in a fixed-dose approach, in accordance to the NICE Clinical Guidelines – Treatment of Depression in Children and Young People [33]. Specifically, the administration of fluoxetine will start at 10 mg daily and will be increased to 20 mg daily after 1 week.

During this second phase (Phase B), participants are free to participate in other treatments such as psychological treatment or psychotherapy (e.g. cognitive behavioural therapy) if medically indicated, and will not be excluded from the study unless the treatment with fluoxetine is stopped. However, these additional treatments will be taken into consideration with the statistical analysis and may lead to post-hoc exclusion of some participants. Under this approach, the data obtained will largely reflect the clinical reality in the sample served.

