## Expected outcomes

### Mood

We expect that ATD-induced mood changes (Phase A) when compared to baseline and BAL administration will be inversely related to the mood-based treatment response to fluoxetine (as assessed via the POMS) and improvements in depressive symptomatology (BDI, HDRS, CDRS-R) 12 weeks into treatment (Phase B). In particular, our assumption is that symptom severity at baseline and change in mood following the ATD challenge will be proportional to mood change due to fluoxetine treatment as response to ATD may be an index of serotonergic vulnerability for mood changes.

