## Discussion

This study may identify a new, simple dietary method to predict treatment response, leading to more targeted pharmacological treatment of adolescents with MDD, and may result in a more rapid treatment response. Children and adolescents may tolerate the ATD/BAL amino acid mixtures better than adults. There have been no serious side effects or complications reported in the studies conducted in minors [12–14, 39]. This study may identify a new, simple dietary method to predict SSRI-related treatment response in terms of serotonergic vulnerability, possibly leading to more targeted pharmacological treatment of adolescents with MDD. In turn, this may lead to a more rapid treatment response and better outcomes. Consequently, adolescents would be able to return to their prior level of functioning earlier, decreasing the overall burden of disease for the individual and allow better integration into the community. Such an approach needs to be confirmed by future larger-scale studies.

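### Phase B has a single open-label fluoxetine arm, so it can show association with improvement during treatment but not prediction of SSRI-specific response

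*Protocol article*

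**What the plan says.** Randomisation concerns Phase A only. According to the Abstract (Methods), "the order in which these conditions (ATD/balanced control condition) occur will be random". For the second phase, the Trial design section states: "In Phase B, this study will employ an open label fluoxetine treatment for a period of 12 weeks". The Phase B section confirms that everyone receives the drug: "Phase B will consist of a 12-week open label pharmacological treatment as usual with the SSRI fluoxetine". Dosing is fixed, visits are weekly, and "participants are free to participate in other treatments such as psychological treatment or psychotherapy (e.g. cognitive behavioural therapy) if medically indicated". The same section adds that such treatments will be considered in the analysis and may lead to later exclusions. No placebo, untreated or other-treatment group is described.

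Three places carry the claim:
- Expected outcomes, Mood: baseline severity and the mood change after ATD "will be proportional to mood change due to fluoxetine treatment".
- Discussion: the study may identify "a new, simple dietary method to predict SSRI-related treatment response in terms of serotonergic vulnerability", with more targeted drug treatment as the intended use. The opening sentence of that section makes nearly the same claim.
- Study objectives and hypotheses: the second objective is to determine whether the ATD mood effect predicts response to the SSRI. The hypothesis that follows is narrower and refers to clinical improvement 12 weeks into treatment.

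The only caveat in the Discussion is that larger studies must confirm the approach.

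**The concern.** Change from before treatment to week 12 in one treated group combines the drug effect with expectation, natural course, regression to the mean, weekly clinical contact and any psychotherapy. A variable associated with that total may be prognostic (these patients improve more, or less, whatever they receive) or predictive of drug benefit (these patients gain more from the drug than from its absence). The intended use, targeting SSRI treatment, needs the second. A positive result from Phase B fits either, but the present wording commits the study to the second reading.

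The prognostic reading is not far-fetched on the article's own evidence. The Background reports that in adults the mood response to ATD predicted depressive episodes over a follow-up year, which is a statement about the course of illness.

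**Working it through.** **1. The article's own figure.** The Power analysis section gives power 0.97 for N = 20, effect size 0.4, alpha 0.05 and critical F 3.26. The numbers of groups (g) and measurements (m) and the correlation (rho) are not stated. With g = 2, m = 3 and rho = 0.5 (inferred), the repeated-measures within-factor formula gives lambda = f² × N × m / (1 − rho) = 0.16 × 20 × 3 / 0.5 = 19.2, df = (2, 36), critical F = 3.259 and power = 0.972. The figure reproduces. It concerns a within-subject mean effect, so it says nothing about a predictor of drug response.

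**2. What one arm identifies.** Let X be the ATD-minus-BAL mood response. Write improvement to week 12 as Y = U + D, where U is the improvement that would have occurred without fluoxetine and D is the change that the drug adds. Then

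Cov(X, Y) = Cov(X, U) + Cov(X, D).

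The data estimate the left side. Separating the two terms on the right needs a predictor-by-treatment interaction, hence a group without the drug. There is one equation with two unknowns, so Cov(X, D) may be zero, equal to the observed covariance, larger than it, or of opposite sign.

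**3. Illustration for the ATD predictor (assumed values).** N = 20, a constant drug effect unrelated to X, and X correlated only with U. The chance of a significant correlation between X and Y (two-sided 0.05; 40,000 simulated trials per row) is set against the Fisher-z power for a true correlation of that size from any source, Φ(atanh(r) × √17 − 1.96) plus a negligible lower tail:

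| Correlation | X related to non-drug improvement only | Fisher-z power |
|---|---|---|
| 0 | 5% | not calculated |
| 0.3 | 25% | 25% |
| 0.5 | 64% | 62% |
| 0.6 | 84% | 82% |

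The columns agree apart from the approximation, as they must: the test sees only the total correlation. A significant result is as likely with no SSRI-specific prediction as with a wholly SSRI-specific one of the same size.

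**4. Baseline severity.** The Mood section also expects severity at baseline to be proportional to change. Let B and F be baseline and follow-up scores with equal variance s², test-retest correlation r and no treatment effect. Then Cov(B, B − F) = s²(1 − r) and Var(B − F) = 2s²(1 − r), so

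Corr(B, B − F) = √((1 − r)/2).

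- r = 0.5: √0.25 = 0.50
- r = 0.7: √0.15 = 0.39
- r = 0.8: √0.10 = 0.32

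The article gives no test-retest correlation, so the r values are assumptions. These figures concern baseline severity only and do not measure any bias in the ATD predictor.

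**5. Could another feature stand in for a comparator?**
- BAL is the control for the Phase A mood effect. All participants go on to fluoxetine whatever the order of the two drinks, so BAL supplies no contrast in Phase B.
- Fluoxetine blood levels are to support preliminary dose-response relationships. Dosing is fixed, levels vary with adherence and metabolism rather than by randomisation, and nobody is unexposed.
- The planned repeated-measures ANOVAs have within-subject factors only.

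**The case against.** The strongest reply is that this is a pilot of 20 with hedged language. The Mood sentence is introduced as an assumption, the Discussion uses conditional wording, and the main hypothesis already speaks of improvement 12 weeks into treatment. Using treatment response to mean improvement under treatment is ordinary usage, and an open-label cohort is a legitimate first step. All of this stands, and it is why the remedy is one of wording and one covariate, with no change of design. It does not cover the attribution of mood change to the drug or the stated aim of targeting SSRI treatment.

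Three stronger readings may tempt a reader, and the article does not support them:
- *General mood lability would explain a positive result.* The predictor is the ATD change compared with baseline and with BAL, under blinding and random order. Lability affects both days and would not by itself produce a systematic ATD-minus-BAL drop. What remains is that true ATD sensitivity could be prognostic.
- *Concurrent psychotherapy is ignored.* The Phase B section says it will be considered in the analysis. That deals with one non-drug source of improvement and leaves the others.
- *The authors propose only larger single-arm studies.* The Discussion does not say what design those studies would have. The gap is that it names size and does not mention a control.

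Severity adjustment may also be specified in an analysis plan that is not shown. That would settle the covariate but leave the wording unchanged.

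**Conclusion.** The point holds as a limit on what may be claimed. Phase B can show whether the ATD-minus-BAL mood response is associated with improvement during fluoxetine treatment. It cannot show whether that response predicts a drug-specific effect, and no analysis of these data can recover the missing contrast.

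No size can be put on the drug-specific part. A reader might infer that it lies somewhere between none and all of the observed association, but even that is not a valid bound (step 2). For baseline severity, a correlation with improvement of about 0.32 to 0.50 can appear with no treatment effect, given assumed test-retest correlations of 0.8 to 0.5 and equal variances. It does not follow that an ATD association would itself be regression to the mean. Nor does it follow that the pilot is invalid or needs another arm.

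**What to change.** 1. Expected outcomes, Mood: describe the change as occurring *during* fluoxetine treatment instead of attributing it to the drug.
2. Discussion: replace the prediction of SSRI-related response with association with improvement during open-label treatment, and bring the similar opening sentence into line. Make the same change to the second objective in Study objectives and hypotheses. The hypothesis after it is already close to supportable.
3. Discussion: state that prognostic and SSRI-specific prediction cannot be separated in this design, and that confirmation needs a controlled study, not only a larger one.
4. Analysis: adjust the ATD-improvement association for pre-treatment severity on one pre-named scale (BDI-II, HDRS or CDRS-R, all collected on the Phase A study days). This deals with regression to the mean that reaches the ATD association through severity. It does not replace a comparator.

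The cost is a less favourable claim and one degree of freedom: in a linear regression with N = 20, the residual degrees of freedom fall from 20 − 2 = 18 to 20 − 3 = 17. No new data are needed.

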### Cognitive parameters, emotional face recognition and reversal learning

We expect that ATD will be associated with an impairment of tests of divided and sustained attention, impaired working memory and alertness. Additionally, we expect an increased negative bias on the facial expression recognition task. Such findings would be in line with well-characterised components of the cognitive profile in depression. ATD will also be expected to enhance prediction of punishment in the used observational reversal learning task.

#### Recruitment

Participants will be recruited mainly via Headspace Services, which is a National Youth Mental Health Foundation that provides early intervention mental health services to 12–25 year olds, and Princess Margaret Hospital. Additionally, local paediatricians, developmental and health services, and general practitioners will participate in identifying suitable participants. Participants who discontinue from the study will be replaced and will be sourced by the same recruitment processes.

#### Blinding procedure and assignment of condition

The randomisation procedure will be managed by the Princess Margaret Hospital Clinical Trials Pharmacy (as of June 2018; Perth Children’s Hospital Clinical Trials Pharmacy). The amino acids will be coded via a number, and this data will then be fed into the randomisation software with the onsite researchers being blind to the challenge given (either ATD or BAL on the respective study day). In addition, the pharmacy will provide a sealed envelope with the coding for each mixture pair (i.e. the ATD/BAL mixture for each subject) and these envelopes will be kept at the study site in case this information is needed. Additional factors will be accounted for by the randomisation software, namely challenge order (ATD on day 1 & BAL on day 2 vs. BAL on day 1 & ATD on day 2), sex (males/females) and BMI (above vs. below the 50th age-adjusted sex-specific BMI percentile). For this study, unblinding is only permissible in the instance of an adverse event.

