#### Phase A

Phase A will consist of two separate study days, where participants will be randomised to either receive the ATD (i.e. an amino acid beverage lacking TRP) or BAL (which will consist of an ATD-based amino beverage plus TRP). Each study day will be separated by a maximum of 7 days. For each study day of Phase A, participants will be required to undertake a drug and pregnancy screen (if female), will be administered the respective amino acid challenge beverages (ATD and BAL), and a series of psychological and cognitive assessments (see below). A total of seven blood samples will also be taken per study day in phase A. The type of assessments and rationale for the blood samples are further described below in more detail.

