#### Data preparation and statistical analysis

The data that will be collected will consist of information relating to medical history, mood, scores on cognitive tasks and blood samples. All data, including blood samples will be de-identified. Codes for the depletion (ATD) and sham depletion (BAL) will be held in an envelope in a securely locked space in the unlikely event of an emergency that requires the code to be broken. Only researchers on the listed research team will have access to the final dataset.

To examine changes in response to ATD (mood, cognitive parameters and tasks, amino acid concentrations, etc.) as well as after treatment (mood symptoms, cognition, SSRI monitoring) a series of repeated measures ANOVAs will be conducted with time (baseline, ATD administration and 12 weeks into treatment) and challenge procedure (ATD/BAL administration) as within-subject factors. We will also evaluate for a significant effect of relevant baseline amino acid levels on the observed changes. If such a significant interaction is discovered, ANCOVAs will be performed with baseline values as covariates.

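### The stated Phase A model has no term for study day or challenge order, so a day-1 to day-2 shift makes the ATD-BAL test conservative, and biases the estimate if the two orders end up unequal

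*Protocol article*

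**What the plan says.** The Trial design section describes Phase A as randomised, double-blind and within-subject. Each participant takes both challenges "on two separate study days, spaced at a maximum of 7 days apart".

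The section on blinding and assignment makes order part of the randomisation, together with sex and BMI: "Additional factors will be accounted for by the randomisation software, namely challenge order". The two orders are ATD then BAL, and BAL then ATD.

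The statistical analysis section then names the model, a series of repeated measures ANOVAs. The factors are "time (baseline, ATD administration and 12 weeks into treatment" and "challenge procedure (ATD/BAL administration) as within-subject factors". The only further adjustment is conditional and concerns baseline values: "If such a significant interaction is discovered, ANCOVAs will be performed with baseline values as covariates". Neither study day nor order is named, and the levels of time do not separate the first study day from the second.

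The Phase A and Phase B assessment sections show that the attention battery, the face task and the reversal learning task are done on both study days. POMS mood ratings are also repeated on both.

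**The concern.** In a two-period crossover, each participant's ATD-BAL difference contains the challenge effect plus or minus any general change from day 1 to day 2. The sign depends on which challenge came first. Repeating the same tasks within a week makes practice or familiarity effects plausible.

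Counterbalancing cancels such a shift in the mean difference only when the two orders are equal in the analysed set. Even then, the shift stays in the spread of the differences unless the model has a term for it. The first objective, the effect of ATD on mood and cognition in 20 adolescents, rests on this contrast.

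**Working it through.** **The plan's own figure.** The Power analysis section gives N = 20, effect size 0.4, α = 0.05, critical F = 3.26 and power 0.97. For within-subject factors the noncentrality is λ = f²·N·m/(1−ρ), with df1 = m−1 and df2 = (N−k)(m−1). With m = 3 measurements, k = 2 groups and ρ = 0.5 (assumed; not stated), λ = 0.16 × 20 × 3/0.5 = 19.2. The critical F(2,36) is 3.259 and power is 0.972, so the stated figures reproduce. One group gives the same power to two decimals, but a critical F(2,38) of 3.245.

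**The two-level contrast.** For ATD against BAL, f = 0.4 means a difference of 2 × 0.4 = 0.8 SD. With ρ = 0.5 the SD of the paired difference is √(2 × 0.5) = 1, so the standardised paired effect is 0.8. Then λ = 0.16 × 20 × 2/0.5 = 12.8, and power on (1,19) df is 0.924.

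**Adding a day shift.** Let π be the day-2 minus day-1 shift, in SDs of the paired difference. Let n₁ participants take ATD first and n₂ take it second. Each difference is 0.8 + π (ATD second) or 0.8 − π (ATD first), plus error with SD 1. Then:

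- Bias of the unadjusted mean difference = π(n₂ − n₁)/N.
- Reported SE relative to its value without a shift = √(1 + π²·[1 − ((n₂ − n₁)/N)²]·N/(N − 1)).

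At 10:10 and π = 0.5 the SE ratio is √(1 + 0.25 × 20/19) = 1.12. Power and alpha below come from 200,000 simulated trials per case. The values of π are assumed.

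| Shift π | SE ratio | Power, no day term | Alpha, no day term | Power, day term |
|---|---|---|---|---|
| 0 | 1.00 | 0.924 | 0.051 | 0.922 |
| 0.2 | 1.02 | 0.918 | 0.046 | 0.923 |
| 0.5 | 1.12 | 0.880 | 0.030 | 0.923 |
| 0.8 | 1.29 | 0.799 | 0.013 | 0.922 |

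The unadjusted estimate is unbiased in every row. Its true standard error is 1/√20 = 0.224 whatever the shift; only the reported one grows.

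**Unequal orders.** At 12:8 the bias is π × 4/20, or 20% of the shift: 0.04, 0.10 and 0.16 SD for the three non-zero shifts. At 13:7 it is π × 6/20, or 30%: 0.06, 0.15 and 0.24 SD. The direction depends on which order is over-represented. With π = 0.5, the 0.8 SD effect is estimated at about 0.70 when 12 take ATD first and about 0.90 when 12 take it second.

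With no ATD effect, the unadjusted alpha stays below 0.05 at 8:12 (0.049, 0.044, 0.037) and rises above it at 7:13 (0.054, 0.065, 0.074). With study day in the model the estimate is unbiased and alpha is about 0.05 throughout. Adjusted power is 0.91 at 12:8 and 0.90 at 13:7.

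**The case against.** **The article may simply be silent.** It condenses a longer protocol, and an analysis plan may exist. Order is a between-subject factor, so it would not be expected in a list of within-subject ones. This stands in part: the omission from the article does not show that order is absent from the full documents. But study day is a within-subject factor, and the article spells out both the factors and the levels of time. The model as stated does not match the design as stated.

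**Mood may be protected.** The expected outcomes for mood compare the ATD response with baseline as well as BAL, and three depression scales are repeated at the start of each study day. If change is taken from a same-day baseline, a constant day-level shift cancels. This stands, and it makes the point weaker for mood. No pre-dose POMS or cognitive measurement is described, so it does not cover the cognitive tasks.

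**Imbalance is not a given.** A reader might infer that replacement and exclusion will make the orders unequal. The documents support only that they may. The randomisation software accounts for order. The Recruitment and Power analysis sections provide for replacements without saying whether a replacement takes over the leaver's order. The post-hoc exclusions in the Phase B section concern additional treatments, and the text does not say that they remove Phase A data. The 12:8 and 13:7 splits are illustrations.

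**The critical F.** A reader might infer from 3.26, which fits two groups, that order was counted in the power calculation and then dropped from the analysis. The protocol gives neither degrees of freedom nor a number of groups. A two-group entry could equally mean that order was intended in the model, so this settles nothing.

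**The study is a pilot**, and it calls its power figures preliminary. That limits the weight of the point, but the remedy is almost free.

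**Conclusion.** The point holds in a limited form. The stated Phase A model leaves out study day and order, although order is built into the randomisation.

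With equal orders the consequence is a conservative test, not a biased one. Power is about 0.92, 0.88 and 0.80 for shifts of 0.2, 0.5 and 0.8 SD, against 0.92 with the day term. A shift of 0.2 SD does almost no harm. It would be tempting to describe this as a smaller effective sample size, but at balance the estimate itself loses no precision. Nor is a general rise in false positives supported: among the splits worked here, alpha exceeds 0.05 only at 7:13.

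Bias arises only if the analysed orders are unequal, at 20% of the shift for 12:8 and 30% for 13:7.

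All sizes rest on assumptions: f = 0.4 read as a 0.8 SD paired difference, correlation 0.5, 20 analysed participants, a constant day shift, and shift sizes that the protocol does not supply. The change should be made, chiefly for the cognitive outcomes.

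**What to change.** In the statistical analysis section, include study day (period) and challenge order (sequence) as fixed effects in the Phase A mood and cognitive models, for example a mixed model with challenge, study day, order and a random participant effect. Report the ATD-BAL difference adjusted for study day. Study day does the work here: an order main effect alone would not take the shift out of the within-participant error. It would also help to state whether a replacement takes over the leaver's order.

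The cost is about one degree of freedom (19 to 18 for the paired contrast). With no shift and 10:10 orders, power goes from 0.924 to 0.922. If the orders are unequal and there is no shift, the adjusted analysis gives up a little more, to about 0.91 at 12:8. No new data are needed. If an unseen analysis plan already has these terms, aligning the protocol text is enough.
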